# Study Protocol

## Title

## Use of Maraviroc (MVC) in immunogical non-responder HIV-1-infected patients

## Rationale

Suboptimal improvement in CD4 cell count is not uncommon in HIV-1-infected patients with suppressed plasma HIV-RNA levels, and a decrease in CD4 cell count in patients with suppressed or low level viremia has been observed.

Although the efficacy of current antiretroviral medications is well established, some antiviral combinations are very effective in suppressing HIV-1 load whereas do not exert any effect on immune reconstitution.

Both T-cell immune activation and fibrosis of peripheral lymphoid tissue could create an environment in which CD4 T cell count decrease in the setting of low or suppressed plasma viremia is likely to occur.

Another fascinating hypothesis, which has still to be elucidated, is that reconstitution of the depleted CD4 pool is blocked by an excess of gp120 HIV-1 protein. This extra-production could be counteracted by an inhibitor of the CCR5 co-receptor that represents one of the major docking tools of HIV-1.

From a clinical point of view, a post-hoc analysis of MERIT study, which compared safety and efficacy of Maraviroc versus Efavirenz in patients who were naïve for antiretroviral therapy, has shown a greater and faster increase of CD4 cells count in patient which were taking Maraviroc than in patients in Efavirenz treatment arm, and this data were statistically significant. Moreover, a larger proportion of patient with less than 200 CD4 cells/µL at baseline has reached or exceeded this threshold in the Maraviroc arm.

In patients who did not reach a virological suppression a minor probability to have AIDS-defining events and an increase of a CD4 cells count have been observed [2].

The increase of CD4 cells count in patients treated with Maraviroc *versus* placebo has been observed also with a different dosage of Maraviroc [3, 4] and in patients with Dual/Mixed or X4-tropic viral strains, in spite of not reaching a virological suppression [5, 6].

However, these observations have been conducted within studies with other primary objectives, while a study with the aim to directly verify this hypothesis has never been performed.

Similar observations have been done in patients who took Enfuvirtide [7], but a possible larger use of this drug has been probably limited by a poor tolerability, particularly due to subcutaneous administration, which causes frequent skin reactions in the injection site. We have chosen Maraviroc because of its ease of use, which makes it more suitable for an intensification strategy in a regimen which had already determined a virological success.

With this in mind, we would like to propose and design a pilot exploratory clinical trial involving a population of HIV-1-infected patients that rapidly reached a virologic suppression without a reconstitution of their immune system.

The chosen dosage of Maraviroc is standard for HIV-infection treatment, after considering necessary modifications according to concomitant medications, as specified in the product data sheet. There are also more data in terms of efficacy and safety for these dosages (from 150mg BID to 600mg BID). The one-year duration of our study is based on the fact that the CD4 cells count increase has been observed in previously reported clinical trials at 48 weeks of treatment. According to this observation, the selected duration would be sufficient to obtain the desired effect.

## Objectives

Primary objectives:

- Evaluate the **clinical (defined as protection from the onset of opportunistic infections) and immunological efficacy** of HAART intensification with MVC as treatment of HIV-1 infection in patients with a CD4 count ≤ 200 cells/L and/or a recovery of CD4 cells < 25% compared to the HAART initiation and with a complete and stable virologic suppression after 12 months of HAART. Patients could also being included if their CD4 slope has been stable without any improvement, with an absolute value around 200 cells/L;
- Evaluate the effects of HAART intensification with MVC on the modification of **immunologic and virologic parameters**;
- Evaluate the **tolerability** of HAART intensification with MVC and the appearance of drug-related side effects.

Secondary objectives:

- Evaluation of intensification treatment of HAART with MVC on modification of following immunological parameters: chemokines-mRNA analysis, helper memory and naïve CD4 lymphocytes, IL-7/IL-7R homeostatic system.

Endpoints

- Simple endpoint: achievement of CD4 count > 200/µL in two consecutive measurements;
- Composite endpoint: CD4 counts > 200/µL and recovery of CD4 > 25% at 2 consecutive time-points (w12 and w48).

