The first parameter (chemokines mRNA) is particularly important since the blockage of cellular co-receptor such ad CCR5 could also influence the process of internalisation of -chemokines. Phenotypes on the cell surface will be evaluated through cytofluorimetry (fluorescein isothiocyanate [FITC], phycoerytrin [PE], and phycoerytrin-cyanin 5 [PCy5]). CD45RA/CD62L/CD4, CD4/CD38, CD8/CD38 in order to measure naïve, memory, and activated CD4+ and CD8+ will be analyzed. The proliferation of T lymphocytes will be evaluated through the quantification of the expression of the Ki67 nuclear antigen in CD4+ and CD8+ cells (an antigen which is expressed during the proliferation phases of cell cycles).

The *ex-vivo* characterization ofsystem IL-7/IL-7R homeostasis will be carried out as well.

If available, a sample before first-line HAART will be analyzed for tropism.

Sample size and statistical analysis

This will be a pilot controlled clinical trial.

Sample size: assuming a proportion of "responder" patients (those patients who achieve, in 2 consecutive measurements, CD4> 200 cells/µL and CD4 lymphocytes recovery > 25 % from baseline, maintaining HIV-RNA <50 copies/mL) of 5% in the control arm, it is expected an absolute increase δ = 20% in the arm of intensification with MVC (responder patients with maraviroc = 25%). We have fixed the study power 1-β = 80% and α = 0.05, thus it is necessary to randomize 50 patients per arm, taking into consideration any protocol violations/lost to follow-up. The threshold of 20% difference between treated with MVC or non-treated is compatible with a proof of efficacy indicated by immunological trials with antagonists of CCR5 co-receptor.

A ​​1:1 randomization in blocks stratified by center will be made.

For statistical analysis, depending on the indication, the following tests will be carried out: chi-square test according to Mantel-Haenszel test, Kruskal Wallis, Log-rank test and Kaplan-Meier analysis model multivariate Cox and logistic regression .

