Comparison of CD4+ and CD8+ count between the study arms A and B and at the different time-points will be assessed by t-test for independent and dependent samples respectively in an intention to treat (ITT) analysis. Statistical evaluation of simple and composite endpoints will be analyzed by binary logistic regression models for the odds ratio estimation and the related 95% confidence intervals. Odds ratios of the MVC arm will be controlled in the regression models for CD4+ counts at baseline. Statistical significance level will be estimated by Wald test and was set at .05 for all of the analyses. In the per-protocol (PP) analysis, patients who dropped the study or switched treatment will be included until their last observation in the randomization arm.

Immunological parameters at baseline (T0), after 12 (w12) and 48 weeks (w48) of MVC intensification will be analyzed with GraphPad 5 PRISM software. Wilcoxon and Mann-Whitney U test will be used. All tests are 2-sided and differences will be considered statistically significant at p<0.05.

Withdrawal from the study

The motivation and the exit date from the study will have to be reported in the medical record of each patient.

The study participants are free to withdraw from the participation at any time, without any explanation and without any prejudice against any and/or future care that should be applied in the Clinical Center where they are followed.

Also, the study participants can be requested to withdraw from the study at any time at the discretion of the investigator, if participation in the study involves any kind of risk for the patient’s health.

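### The between-arm comparison of the continuous CD4 count is planned as an unadjusted t-test and is not a named endpoint; baseline-adjusted ANCOVA would be more powerful at no cost

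*Protocol*

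**What the plan says.** Under Objectives, the Endpoints list has two entries: "Simple endpoint: achievement of CD4 count > 200/µL in two consecutive measurements" and "Composite endpoint: CD4 counts > 200/µL and recovery of CD4 > 25% at 2 consecutive time-points (w12 and w48". Both are responder yes/no variables.

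Under Sample size and statistical analysis, the size of 50 per arm rests on a responder proportion "of 5% in the control arm, it is expected an absolute increase δ = 20% in the arm of intensification with MVC", that is 5% v 25%, with "study power 1-β = 80% and α = 0.05". The responder defined there must meet both CD4 conditions and must also be "maintaining HIV-RNA <50 copies/mL".

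For analysis, the same section states: "Statistical evaluation of simple and composite endpoints will be analyzed by binary logistic regression models for the odds ratio estimation". The odds ratio for the maraviroc arm is adjusted for baseline CD4 and tested by the Wald test. CD4 and CD8 counts are compared between arms, by intention to treat, with a t-test for independent samples. No baseline adjustment is mentioned for that comparison, and it is not listed as an endpoint.

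**The concern.** The hypothesis is largely about the size of the CD4 rise. The Rationale cites greater CD4 increases with maraviroc and sets the trial's length on the same ground: "The one-year duration of our study is based on the fact that the CD4 cells count increase has been observed" at 48 weeks in earlier trials. Neither listed endpoint measures that rise. A patient who goes from 60 to 190 cells/µL counts as a non-responder, exactly like one who does not move.

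The one analysis that does use the full scale is the weaker of two available. Comparing raw follow-up counts leaves the between-patient spread in baseline CD4 in the error term. The plan already treats baseline CD4 as worth adjusting for in the logistic models, so leaving it out here is inconsistent. In a 100-patient pilot trial, the full-scale comparison could miss a CD4 effect that the same data would show once adjusted.

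**Working it through.** **Inputs from the protocol.** 5% v 25% responders, 80% power, α = 0.05, 50 per arm, 1:1. I take the test as two-sided, which the protocol states for the immunological parameters.

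**Inputs assumed.** The protocol gives no mean, SD or correlation for CD4. I assume baseline mean 150-170 cells/µL, baseline SD 40-50 and SD of change 40-50, with a wider range shown in step 3.

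**1. The plan's own figure.** With pooled variance, mean proportion 0.15:

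n = [1.96·√(2·0.15·0.85) + 0.84·√(0.05·0.95 + 0.25·0.75)]² / 0.20² = (0.990 + 0.408)² / 0.04 ≈ 49 per arm.

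This agrees with the stated 50. At 50 per arm, power is 80.9% by this approximation. By exact enumeration it is 85.2% for the uncorrected chi-square test and 73.9% for an unadjusted Wald test of the log odds ratio.

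**2. What 50 per arm detects on the full scale.** (1.96 + 0.84)·√(2/50) = 2.80 × 0.20 = 0.56 SD. With the t distribution it is about 0.57 SD (power 80.6%), before any baseline adjustment.

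**3. Raw counts against baseline-adjusted counts, all patients benefiting.** Let follow-up CD4 be baseline plus an independent change. Find the mean changes that give 5% and 25% responders under the joint rule (above 200 and more than 25% above baseline, at both visits). Call the arm difference Δ. The raw t-test sees Δ/√(SD_b² + SD_c²). An analysis of change sees Δ/SD_c, and in this model ANCOVA has nearly the same power. At 50 per arm:

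| Baseline mean | SD_b | SD_c | Δ | Raw effect | Raw power | Change effect | Change power |
|---|---|---|---|---|---|---|---|
| 150 | 40 | 40 | 39.5 | 39.5/56.6 = 0.70 | 93.3% | 39.5/40 = 0.99 | 99.8% |
| 170 | 50 | 50 | 47.2 | 47.2/70.7 = 0.67 | 91.1% | 47.2/50 = 0.94 | 99.7% |
| 150 | 40 | 60 | 57.1 | 57.1/72.1 = 0.79 | 97.5% | 57.1/60 = 0.95 | 99.7% |
| 150 | 50 | 30 | 31.3 | 31.3/58.3 = 0.54 | 75.8% | 31.3/30 = 1.04 | 99.9% |

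The first two rows lie in the assumed range; the last two widen it. The advantage runs from about 2 points, when changes are large relative to the baseline spread, to about 24 points, when they are small.

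**4. If only some patients benefit.** Simulation under the assumed distributions, again calibrated to 5% v 25% responders:

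| Share of maraviroc patients who benefit | ANCOVA v raw t-test | ANCOVA v responder chi-square (about 85%) |
|---|---|---|
| All | 99.8-100% v 91-94% | gain of about 15 points |
| Half | not tabulated | gain of about 4 to 7 points |
| A quarter | 76-79% v 54-59% | loss of about 6 to 10 points |

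So ANCOVA beats the planned t-test whether the effect is shared by all or by a quarter. Its advantage over the responder test depends on how widely the effect is shared.

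**The case against.** The strongest reply is that the responder endpoints are a coherent choice. The cuts at 200 cells/µL and 25% reverse the eligibility criteria, so they ask whether a patient leaves the state that defined a non-responder. The Rationale also cites a result at the 200 threshold in the trial against efavirenz. The responder used for the sample size includes viral suppression, which a mean CD4 difference would not capture. All of this stands, and it is why the responder endpoints should stay.

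A reader might go further and infer that the cut throws away most of the CD4 information and costs some 13 to 25 points of power under the plan's own 5% v 25%. The documents do not support that. Those figures need a normal distribution, equal SDs and an effect shared by nearly all patients, none of which the protocol states. If a quarter benefit, the responder chi-square test is the more powerful one. Nor is full-scale CD4 discarded: a between-arm comparison of counts is planned. A reader might also suppose that patients with the lowest counts cannot reach 200 within a year; nothing in the protocol says so.

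A separate analysis plan might specify adjustment. But the protocol itself fixes the t-test, so the point is not one that it merely leaves open.

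**Conclusion.** The point holds as an improvement, not as an error in the design. Full-scale CD4 is compared by a test that ignores a covariate the plan already collects and uses elsewhere, and that comparison has no standing as an endpoint. Under the assumed CD4 distributions, ANCOVA adds about 6 to 9 points of power over the raw t-test if all patients benefit and about 17 to 25 points if a quarter do. With the wider SDs in the table the all-benefit gain runs from about 2 to 24 points. These figures are conditional on assumptions that the protocol neither gives nor contradicts. The direction is safer than the size: with an appreciable correlation between baseline and follow-up CD4, adjustment helps.

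Making full-scale CD4 the deciding endpoint is a trade-off for the sponsor, since the comparison with the responder test changes sign with the share of patients who benefit.

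**What to change.** Under Sample size and statistical analysis, replace the between-arm t-test on CD4 by ANCOVA of week-48 CD4 (or change from baseline) with arm and baseline CD4 in the model. Report the adjusted mean difference with its 95% confidence interval.

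Under Endpoints, name this as an efficacy endpoint beside the simple and composite responder endpoints, which stay as they are, and say which endpoint decides the trial.

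In the sample-size paragraph, add that 50 per arm detects a difference of about 0.57 SD with 80% power before baseline adjustment.

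The cost is wording only. No patients, visits or assays are added: CD4 is already planned for analysis at baseline and follow-up, and baseline CD4 is already a planned covariate.

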## Design

This will be a randomised, multicenter, study that will evaluate HAART intensification with MVC as treatment of HIV-1 infection in patients with a CD4 count ≤ 200 cells/L and/or a recovery of CD4 cells < 25% compared to the HAART initiation and/or a stable CD4 slope without any improvement, with an absolute value around 200 cells/L and with a complete and stable virologic suppression after 12 months of HAART. Among the adult HIV-1 infected patients screened, 50 patients will be randomized in arm A (HAART + MVC) and 50 in arm B (HAART without MVC), in a 1:1 fashion.

Treatment regimen

Maraviroc dosing schedule is: from 150mg to 600mg BID, according to the other antiretroviral drugs in the patient.s therapy. Maraviroc will be administered at the dosing regimen of 150mg BID with nelfinavir and protease inhibitors boosted by ritonavir (PI/r), as example atazanavir/rtv, darunavir/rtv, lopinavir/rtv e saquinavir/rtv; 300mg BID with nevirapine, fosamprenavir/rtv, tipranavir/rtv, raltegravir and enfuvirtide (T-20); 600mg BID with efavirenz and etravirine. In the case of administration within a regimen including a PI/rtv (atazanavir/rtv, darunavir/rtv, lopinavir/rtv e saquinavir/rtv), MVC dosage will be always 150mg BID.

Study population

The enrollment of 100 continuously observed patients, with the characteristics mentioned above, at Clinical Science Department, Division of Infectious Diseases and Immunopathology of Università degli Studi, “L. Sacco” Hospital, Milan, is expected after EC/IRB approval.

Other clinical centers will participate to the study: Clinic of Infectious Diseases, “San Paolo” Hospital: Prof.ssa [name]; 1a and 2a Division of Infectious Diseases, “L. Sacco” Hospital, Milan: [name]; Clinic of Infectious Diseases, Scientific Institute “San Raffaele” Hospital, Milan: [name]; Clinic of Infectious Diseases, University of Brescia: [name]; Clinic of Infectious Diseases, University Tor Vergata, Rome: [name]; Clinic of Infectious Diseases, University of Turin: [name] [name]; National Institute of Infectious Diseases, “L. Spallanzani” Hospital, Rome: [name]; Clinic of Infectious Diseases, “San Gerardo” Hospital, Monza: [name].

The enrollment will include 100 HIV-positive patients, with CD4+ lymphocyte count ≤200 cells/µL and/or CD4+ cells count recovery ≤25%, with suppressed viraemia (HIV-RNA <50 cp/mL) after 12 months of antiretroviral drugs. It will be possible also to enroll patient with stable CD4+ count without any improvement, with an absolute value around 200 cells/ µL.

**Study Methodology**

Clinical evaluation.

At baseline, at weeks 2, 4, 8, 12 from the beginning of the study, following 4, 6 and 9 months from the beginning of the study and at the end of the period of administration of MVC:

- Clinical History;
- Physical Examination;
- Evaluation of Karnofsky index

Blood tests

At enrollment and subsequently at weeks 2, 4, 8, 12 from the beginning of the study, and then at 4, 6 and 9 months from the beginning of the study and at the end of the period of administration of MVC:

- Examination of complete blood cell count with differential;
- Blood tests: glucose, urea nitrogen, creatinine, electrolytes, transaminases, GT, direct and indirect bilirubin, amylase, LDH, CPK, sieroprotein electrophoresis, hsPCR, total cholesterol and HDL;
- Pregnancy test at enrolment.

Virological evaluation

At screening and in case of virologic failure during the protocol, it will be performed a blood test to get 2 aliquots of 5x10^6 frozen viable cells in order to perform the sequence of the gp120 gene and subsequent determination of viral tropism by algorithm .

It will also be required, where available, plasma stored under appropriate conditions, from the patient when in a condition of detectable viremia (2 mL of plasma required to perform the test Trofile post-hoc).

At baseline and after 2, 4, 8 and 12 weeks after start of the study, and then at 4, 6 and 9 months from the beginning of the study and at the end of the period of administration of MVC:

- Quantification of HIV-RNA.

Immunological evaluations

At baseline and after 2, 4, 8, 12 weeks after start of the study, then at 4, 6 and 9 months from the beginning of the study and at the end of the period of administration of maraviroc:

- Immunophenotypic analysis (lymphocytes memory and naïve CD4 & CD8);

- Analysis of chemokine mRNA;

- Analysis of the levels of plasma IL-7/IL-7R.

The first parameter (chemokines mRNA) is particularly important since the blockage of cellular co-receptor such ad CCR5 could also influence the process of internalisation of -chemokines. Phenotypes on the cell surface will be evaluated through cytofluorimetry (fluorescein isothiocyanate [FITC], phycoerytrin [PE], and phycoerytrin-cyanin 5 [PCy5]). CD45RA/CD62L/CD4, CD4/CD38, CD8/CD38 in order to measure naïve, memory, and activated CD4+ and CD8+ will be analyzed. The proliferation of T lymphocytes will be evaluated through the quantification of the expression of the Ki67 nuclear antigen in CD4+ and CD8+ cells (an antigen which is expressed during the proliferation phases of cell cycles).

The *ex-vivo* characterization ofsystem IL-7/IL-7R homeostasis will be carried out as well.

If available, a sample before first-line HAART will be analyzed for tropism.

Sample size and statistical analysis

This will be a pilot controlled clinical trial.

Sample size: assuming a proportion of "responder" patients (those patients who achieve, in 2 consecutive measurements, CD4> 200 cells/µL and CD4 lymphocytes recovery > 25 % from baseline, maintaining HIV-RNA <50 copies/mL) of 5% in the control arm, it is expected an absolute increase δ = 20% in the arm of intensification with MVC (responder patients with maraviroc = 25%). We have fixed the study power 1-β = 80% and α = 0.05, thus it is necessary to randomize 50 patients per arm, taking into consideration any protocol violations/lost to follow-up. The threshold of 20% difference between treated with MVC or non-treated is compatible with a proof of efficacy indicated by immunological trials with antagonists of CCR5 co-receptor.

A ​​1:1 randomization in blocks stratified by center will be made.

For statistical analysis, depending on the indication, the following tests will be carried out: chi-square test according to Mantel-Haenszel test, Kruskal Wallis, Log-rank test and Kaplan-Meier analysis model multivariate Cox and logistic regression .

Comparison of CD4+ and CD8+ count between the study arms A and B and at the different time-points will be assessed by t-test for independent and dependent samples respectively in an intention to treat (ITT) analysis. Statistical evaluation of simple and composite endpoints will be analyzed by binary logistic regression models for the odds ratio estimation and the related 95% confidence intervals. Odds ratios of the MVC arm will be controlled in the regression models for CD4+ counts at baseline. Statistical significance level will be estimated by Wald test and was set at .05 for all of the analyses. In the per-protocol (PP) analysis, patients who dropped the study or switched treatment will be included until their last observation in the randomization arm.

Immunological parameters at baseline (T0), after 12 (w12) and 48 weeks (w48) of MVC intensification will be analyzed with GraphPad 5 PRISM software. Wilcoxon and Mann-Whitney U test will be used. All tests are 2-sided and differences will be considered statistically significant at p<0.05.

Withdrawal from the study

The motivation and the exit date from the study will have to be reported in the medical record of each patient.

The study participants are free to withdraw from the participation at any time, without any explanation and without any prejudice against any and/or future care that should be applied in the Clinical Center where they are followed.

Also, the study participants can be requested to withdraw from the study at any time at the discretion of the investigator, if participation in the study involves any kind of risk for the patient’s health.

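### The 80% power stated for 50 patients per arm fits an uncorrected chi-square test; the Wald test that the protocol fixes gives about 74% before losses and cannot reject if no control patient responds

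*Protocol*

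**What the plan says.** The Design section gives the allocation: "50 patients will be randomized in arm A (HAART + MVC) and 50 in arm B (HAART without MVC), in a 1:1 fashion". Under Sample size and statistical analysis, a responder must have CD4 above 200 cells/µL and a recovery above 25% on two consecutive measurements while HIV-RNA stays below 50 copies/mL. The responder proportion is assumed to be "of 5% in the control arm", and for the other arm "it is expected an absolute increase δ = 20% in the arm of intensification with MVC (responder patients with maraviroc = 25" (in per cent). The error rates are set next: "We have fixed the study power 1-β = 80% and α = 0.05". From these inputs the protocol derives the number to randomise: "thus it is necessary to randomize 50 patients per arm, taking into consideration any protocol violations/lost to follow-up". No formula, reference test or loss rate is given.

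The same section lists several tests to be used as the indication requires, among them a Mantel-Haenszel chi-square, without tying that test to an endpoint. The paragraph that follows does make an assignment: the simple and composite endpoints go to binary logistic regression, with the treatment odds ratio adjusted for baseline CD4, and "Statistical significance level will be estimated by Wald test and was set at .05 for all of the analyses". It names no alternative for an arm without responders.

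**The concern.** At a 5% control rate the control arm is expected to contain 50 × 0.05 = 2.5 responders. With so few events the standard error of the log odds ratio is large, and the Wald statistic falls below the chi-square statistic for the same table. With no control responders the estimate and its standard error both diverge, and the Wald p-value goes towards 1.

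Two things are at stake. A true effect of the planned size would be missed more often than the stated 20%. And one of the most favourable patterns, no control responders against many on maraviroc, would come out of the planned test as non-significant with an unusable odds ratio. Choosing another test after seeing that table would be a data-driven change.

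**Working it through.** **Inputs.** From Sample size and statistical analysis: 5% and 25% responders, 80% power, alpha 0.05, 50 per arm. Two-sidedness is stated in the paragraph on immunological parameters ("All tests are 2-sided and differences will be considered statistically significant at p<0.05") and is assumed to apply here too. Loss rate: not given; 0% and 10% are shown, with losses taken to reduce the evaluable number.

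**Step 1, reproduce the plan's figure.** Pooled two-proportion formula, mean rate 0.15:

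n = [1.96 √(2 × 0.15 × 0.85) + 0.842 √(0.05 × 0.95 + 0.25 × 0.75)]² / 0.20² = 48.8, so 49 per arm.

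The stated 50 is therefore reproduced as an uncorrected chi-square calculation. Other formulas give 47 (unpooled), 45 (arcsine), 59 (continuity-corrected) and 39 (one-sided; 48 with continuity correction).

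**Step 2, power of each test.** Let X ~ Bin(n, 0.05) on control and Y ~ Bin(n, 0.25) on maraviroc. Power is the sum of P(X = x) × P(Y = y) over all tables that the test calls significant.

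- Wald: z = ln[y(n − x) / (x(n − y))] / √[1/x + 1/(n − x) + 1/y + 1/(n − y)], significant if |z| > 1.96. Tables with a zero cell count as non-significant.
- Mantel-Haenszel, unstratified, no continuity correction: (N − 1)D² / [n² t (N − t)] > 3.84, with D = y(n − x) − x(n − y), N = 2n, t = x + y.

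| Test | 50 per arm | 45 per arm |
|---|---|---|
| Wald, logistic | 73.9% | 65.9% |
| Mantel-Haenszel, continuity-corrected | 74.6% | 67.9% |
| Mantel-Haenszel, uncorrected | 83.6% | 80.7% |
| Pearson chi-square, uncorrected | 85.2% | 81.3% |

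Wald power is 79.7% at 56 per arm and 80.9% at 57, so 57 evaluable per arm are needed for 80%. Uncorrected Mantel-Haenszel power is 79.6% at 44 and 80.7% at 45, so 45 suffice.

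**Step 3, where the Wald test loses power.** P(X = 0) = 0.95^50 = 7.7% (0.95^45 = 9.9% at 45 per arm). At 0/50 against 12/50, D = 12 × 50 = 600, and the Mantel-Haenszel statistic is 99 × 600² / (2500 × 12 × 88) = 13.5, far above 3.84; the Wald test cannot reject. The gap between the two tests at 50 per arm is 83.6 − 73.9 = 9.7 points. Nearly all tables with X = 0 are significant by Mantel-Haenszel, so about 7.7 of those points come from the zero cell. The other 2 or so come from tables with very few control responders. For example, 1/50 against 7/50 gives Wald z = ln(7 × 49 / 43) / √(1 + 1/49 + 1/7 + 1/43) = 2.08 / 1.09 = 1.91, not significant, while Mantel-Haenszel gives 99 × 300² / (2500 × 8 × 92) = 4.84, significant.

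**Step 4, does the planned covariate rescue the Wald test?** In 6,000 simulated trials per setting, with an assumed log odds ratio of 0, 0.5 or 1.0 per SD of baseline CD4, adjusted Wald power is 74.0%, 74.8% and 76.9% at 50 per arm, and 65.2%, 66.8% and 69.9% at 45. It does not reach 80% over this range.

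**Step 5, direction of the error.** With both rates at 5% the Wald test's type I error is 0.2%; with both at 15% it is 4.0%. The test is conservative.

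**The case against.** The strongest reply is that the sample size is right. It is reproduced by the standard formula, and an uncorrected chi-square test exceeds 80% at 50 per arm and still does at 45. That stands. A reader might infer that the trial is under-sized or that 50 is an arithmetic error; the documents do not support either. The fault is that the size suits one test and the analysis names another.

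A reader might also infer from 49 against 50 that only one patient per arm is left for losses. That depends on one approximate formula which the protocol does not say it used. Under exact chi-square power the allowance is about 10%, so this charge is not made.

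It can be said that the Mantel-Haenszel test is already listed. It is, but with no endpoint attached, while the responder endpoints are expressly given to logistic regression and the Wald test. The list does not resolve the mismatch.

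It would be tempting to apply the power figures to the simple endpoint (CD4 above 200 alone). The protocol gives no control rate for it, and it is a less demanding criterion, so the figures cover the composite responder endpoint only.

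Finally, this is a pilot, the error is conservative, and a statistical analysis plan that is not shown might contain a rule for zero cells. These points lower the severity. They do not remove the mismatch, because the protocol itself both states the power and names the test.

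**Conclusion.** The concern holds as a mismatch between the sample-size statement and the fixed test. For the composite responder endpoint at 5% against 25%, two-sided 0.05, the planned Wald test has 73.9% power at 50 per arm with no losses, about 6 points below the stated 80%, and 65.9% with 10% loss. In 7.7% of such trials the control arm has no responders and the test cannot reject.

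This rests on the protocol's own rates, on a two-sided test, on zero-cell tables being counted as non-significant, and on an assumed 10% loss for the lower figure. The strength of baseline CD4 as a predictor is also assumed, and over the range tried it does not change the conclusion. There is no inflation of false positives. The point should be fixed, but it does not undermine the design.

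**What to change.** 1. For the composite responder endpoint, replace the Wald test by the Mantel-Haenszel chi-square already listed, state that it is without continuity correction, and name it as the decisive test. The omission of the correction must be explicit: the corrected version has 74.6% power at 50 per arm and would leave the shortfall in place.
2. Report the baseline-CD4-adjusted odds ratio as a supporting estimate by a method that stays finite with a zero cell, such as Firth logistic regression with profile penalised-likelihood limits. The ordinary likelihood-ratio test is not a safe substitute: its simulated type I error was about 9% with both rates at 5%.
3. Restate the sample-size sentence with test, evaluable number and loss rate. Unstratified Mantel-Haenszel power is 83.6% at 50 and 80.7% at 45 evaluable per arm, so 50 randomised covers (50 − 45)/50 = 10% loss. If the test is stratified by centre, the figure should be confirmed for the expected centre sizes.
4. If the Wald test is kept, state about 74% power before losses and add a rule for an arm with no responders.

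The cost is a rewording of the test and sample-size sentences and one standard software option, with no extra patients. The downside is small: the decisive p-value is not adjusted for baseline CD4 and may differ from the adjusted odds ratio, so the protocol should say that the former decides.
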